## Methods

### Study design

A multicentre non-blinded superiority randomised controlled trial on VAC vs. ROD. Danish, as well as other European centres, will be invited to participate. The study protocol adheres to the guidelines determined in Standard Protocol Items: Recommendations for Interventional Trials (SPIRIT) (Additional file 2) [45].

The VACOR study will include two separate studies: VACOR-Main and VACOR-Microdialysis.

All centres must participate in the VACOR-Main study, with only Odense University Hospital participating in the VACOR-Microdialysis study. VACOR-Main will report on all primary and secondary outcomes; in VACOR-Microdialysis, a sub-study of 10 patients from each group will be included. A microdialysis catheter will be placed in the peritoneal cavity, and samples of the peritoneal fluid will be collected every 6th hour to measure the concentration of lactate, glucose, pyruvate, glycerol, cytokines (IL-1b, IL-6, IL-10, TNF-a) and metalloproteins (MMP9 and MMP8). The purpose is to investigate intraperitoneal metabolic changes and inflammatory responses in the two groups.

### In-hospital healthcare utility

Three months after the index operation, a record review will be made to estimate the healthcare utility. All data will be retrieved from the electronic patient system and include surgeries, total hospital stay, admissions to the ICU, and radiological interventions (Table 2). For the analysis, unit costs were obtained from the Danish Health Authority. The diagnosis-related groups (DRG) will be used, which express the hospital's average operating expenses within each DRG group. To ensure comparability between centres, we will utilise the Danish costs for both Danish and international patients.

### Study population

#### Inclusion criteria

Patients eligible for enrolment are 18 + years of age and scheduled for acute laparotomy due to suspected peritonitis originating from perforation of the small bowel, colon, or rectum. To be included, purulent, enteric, or faecal contamination in a minimum of 2 out of 4 quadrants must be confirmed.

#### Exclusion criteria

Diffuse peritonitis originating from a perforation on the stomach, duodenum, gallbladder, appendix, necrotising pancreatitis, salpingitis, or peritoneal dialysisPrimary peritonitisImmunocompromised (history of steroid or biological treatment within the last three months or previous organ transplantation)Chronic parenchymal liver disease (chronic liver disease with plasma bilirubin above 35 mmol/L)PregnancyPatients with end-stage disease (metastatic disease)Laparoscopic surgery (not converted to laparotomy)Acute occlusion of superior mesenteric arteryPeritoneal carcinomatosisAbdominal traumaLack of consent from the surgical equipoiseLocal peritonitis confined to one quadrant only

### Study setting

The study will be conducted in general surgery departments, emergency departments, and operating theatres. The lead centre is Odense University Hospital in Odense, Denmark, a tertiary referral academic medical centre. Other recruiting sites will include academic and community hospitals located in Europe, familiar with the interventions and willing to adhere to the treatment regimens.

### Randomisation

Patients are included by a surgical equipoise followed by patient information and consent after recovery. The on-call surgeon will contact the primary investigator from each site when a patient is scheduled for diagnostic laparoscopy or explorative laparotomy on suspicion of secondary peritonitis. Patients fulfilling the inclusion criteria will be randomised after consent has been obtained by the surgical equipoise (Fig. 1). This could occur before, during, or at the end of index laparotomy, disclosing a complete overview of all potential candidates. Most patients will be able to receive both treatments regardless of what arm they are allocated without changing the treatment regimen. However, there will be some exceptions where it is necessary to modify or change the surgical treatment, irrespective of the randomisation allocation. Centres that do not receive approval from their respective scientific ethics committee to include patients through a surgical equipoise must obtain informed and written consent before randomisation. Randomisation will be web-based via (REDCap ®) in blocks of 2, 4, and 6 stratified for centre and age above or below 65 years. The justifications for stratifying according to the centre are that there might be differences in the surgical treatment, preoperative optimisation, and postoperative treatment, both in the ward and intensive care unit (ICU), which might affect the outcome. The patients will be randomised to either abdominal closure with ROD or open abdomen with VAC according to transparent reporting of trials (CONSORT) (Fig. 2). The randomisation tool and eligibility criteria can be accessed through our website, www.vacor.sdu.dk.

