**Methods:**

This study will be a randomised controlled multicentre trial, including patients aged 18 years or older with purulent or faecal peritonitis confined to at least two of the four abdominal quadrants originating from the small intestine, colon, or rectum. Randomisation will be web-based to either primary closure with ROD or VAC in blocks of 2, 4, and 6. The primary endpoint is peritonitis-related complications within 30 or 90 days and one year after index operation. Secondary outcomes are comprehensive complication index (CCI) and mortality after 30 or 90 days and one year; quality of life assessment by (SF-36) after three and 12 months, the development of incisional hernia after 12 months assessed by clinical examination and CT-scanning and healthcare resource utilisation. With an estimated superiority of 15% in the primary outcome for VAC, 340 patients must be included. Hospitals in Denmark and Europe will be invited to participate.

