**Fig. 2 Fig2:**
[figure not shown]
CONSORT flow diagram

In cases where the surgeon finds that the allocated treatment may be contraindicated or is judged to harm the patient, it will be left to the surgeon's discretion to choose the most appropriate treatment. In cases where the bowels are left stapled in discontinuity as a part of the damage control principle, the patient's fascia cannot be closed due to swelling or the presence of abdominal compartment VAC treatment may be applied irrespective of the randomisation. These patients remain in the trial for an intention-to-treat and per-protocol analysis. By excluding such patients, there might be a risk of selection bias. Any eligible patient not included will be registered in a screening log.

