#### Sample size and power

With an expected peritonitis-related complications rate of 40% in the ROD group [20] and 25% in the VAC group [42, 44], the desired power of 80%, a significance level of 0.05, and an expected drop-out of 5%, a total of 340 patients should be included.

As the CCI distribution in this group of patients is unknown, we could not perform an explicit sample size calculation for this secondary outcome. A 0.32 standard deviation difference in mean CCI between the two groups could be detected with 80% power with this sample size.

To ensure sufficient recruitment, the study will be multicentre and European. Eight active centres have been included, and two are in process. Randomisation tools along with eligibility criteria are accessible through our website. The workflow and relevant contact details appear on posters at the participating departments. Study progress will be available on the website.

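### Published blocks of 2, 4 and 6 within centre-by-age strata let anyone who knows earlier allocations predict the next arm above chance, in an open trial with a consent step at entry

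*Protocol article*

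**What the plan says.** Under Study design, the Protocol article describes "A multicentre non-blinded superiority randomised controlled trial on VAC vs. ROD". Treatment allocations are thus visible on site once given.

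The abstract gives the block sizes: "Randomisation will be web-based to either primary closure with ROD or VAC in blocks of 2, 4, and 6". The Randomisation section repeats them and adds the strata: "in blocks of 2, 4, and 6 stratified for centre and age above or below 65 years".

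On entry, the same section says: "Patients fulfilling the inclusion criteria will be randomised after consent has been obtained by the surgical equipoise". The exclusion criteria list lack of that consent as a reason not to include a patient. The moment of randomisation is left open: "This could occur before, during, or at the end of index laparotomy". On local organisation, "The on-call surgeon will contact the primary investigator from each site" when a patient is scheduled for surgery on suspicion of secondary peritonitis.

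The safeguards stated are web-based allocation through REDCap, more than one block size, and a log, described after the CONSORT figure: "Any eligible patient not included will be registered in a screening log".

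Under Statistical analysis, the primary outcome is compared by a chi-square test. A separate logistic regression adjusts for age, performance status and comorbidity.

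**The concern.** Permuted blocks force the arms back into balance, so past allocations carry information about the next one. The smaller the blocks and the finer the strata, the stronger that information. It becomes usable when three things coincide: past allocations are visible, the block sizes are known, and somebody may still decide whether the next patient enters. The first two hold here by design and by publication. The third is plausible because entry depends on consent by the surgical equipoise, which may be sought after the abdomen has been opened.

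At stake is selection bias. If patients with worse sepsis or a worse abdomen were entered more readily when one arm was expected, the arms would differ in severity from the start. The unadjusted primary test would carry that difference into the result. The planned covariates would not remove it, since none of them measures severity of sepsis or the state of the abdomen.

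**Working it through.** The document gives no figure for predictability, so there is none to reproduce. The check asks how well an observer can guess the next arm.

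**Inputs from the document**
- Block sizes 2, 4 and 6, stratified by centre and two age groups (Randomisation).
- Total sample size 340 (Sample size and power).
- Centres: "Eight active centres have been included, and two are in process" (Sample size and power).

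**Assumptions**
- The three sizes are equally likely and in random order; the article states neither.
- Recruitment is equal across strata. 8 centres × 2 age groups = 16 strata, and 340/16 ≈ 21 patients each. 10 × 2 = 20 strata, and 340/20 = 17 each.
- The observer knows the block sizes and all earlier allocations in the stratum, and guesses the likelier arm.

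**First patients in a new stratum (exact)**

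In a block of size b, after one allocation, the opposite arm follows with probability (b/2)/(b − 1).
- Sizes 2, 4, 6: (1 + 2/3 + 3/5)/3 = 34/45 = 76%.
- Sizes 4, 6, 8: (2/3 + 3/5 + 4/7)/3 = 61%.

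After two patients in the same arm, size 2 is ruled out. The chance of two in a given arm is 1/2 × 1/3 = 1/6 for size 4 and 1/2 × 2/5 = 1/5 for size 6, so the weights are 5/11 and 6/11. The opposite arm then follows with probability 5/11 × 1 + 6/11 × 3/4 = 9.5/11 = 86%. After three in the same arm, only size 6 is possible and the next allocation is certain.

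**Whole strata (simulation)**

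8,000 strata of 17 and 8,000 of 21 patients were simulated. The observer's probabilities were updated by Bayes' rule after each allocation. Ranges cover the two stratum lengths and repeat runs.

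| Measure | Sizes 2, 4, 6 | Sizes 4, 6, 8 (known to the observer) |
|---|---|---|
| Best guess correct (chance: 50%) | 69% | 66-67% |
| Predictable with at least 2/3 confidence | 56-57% | 54-56% |
| At least 75% | 56-57% | 37% |
| At least 80% | 45-47% | 19-21% |
| At least 90% | 6-7% | 4% |
| Certain | 4% | 2% |

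With 2, 4 and 6, more than half of the allocations can be predicted with at least 75% confidence, but few with certainty. Changing the sizes to 4, 6 and 8 makes almost no difference at the 2/3 cut-off. It roughly halves the share at 80% or more and lowers overall correct guesses by only 2 to 3 percentage points. If the sizes are known, larger blocks alone therefore give a modest gain.

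**The case against.** Mixed block sizes with central web-based allocation are a conventional choice, and the mixing works: a known fixed size of 2 would make 47% of allocations certain, against about 4% here. This stands. A reader might infer that the next arm is usually known, and the figures do not support that.

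A reader might also infer that the site's primary investigator decides who enters and keeps track of the sequence. The document says only that this person is contacted about candidates. It does not say who gives the equipoise consent or that anyone follows past allocations, and the figure showing the consent flow is not available. Centres without ethics approval for this route must obtain written consent before randomisation instead. The prediction mechanism is therefore plausible, not documented, and nothing shows that selective entry has occurred.

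There are safeguards. The screening log could expose selective entry, although it detects rather than prevents, and a patient refused under the equipoise criterion might not count as eligible and so might not be logged. Preoperative SOFA and the Mannheim peritonitis index are recorded, so an imbalance in severity could be seen. After allocation, the surgeon may depart from the assigned treatment where it is judged contraindicated or harmful, and the patient stays in the intention-to-treat analysis. That weakens the motive to decline entry but does not remove it.

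Finally, how the sequence is ordered and concealed is detail that an article may leave to the full protocol. This also stands. The point rests only on what the article fixes and discloses: the sizes, the strata and the open design.

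**Conclusion.** The point holds as a limited design weakness with a cheap remedy. In an open trial with a consent step at entry, the published scheme lets anyone who knows a stratum's history guess correctly about 69% of the time, with at least 75% confidence for 56-57% of allocations and with certainty for about 4%. These figures rest on equally likely, randomly ordered sizes, strata of 17 to 21 patients and complete knowledge of earlier allocations.

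They measure the opportunity for selection, not its effect: no bias in the treatment comparison has been quantified, and none is alleged. The opportunity is worth closing because the primary test is unadjusted and selective entry cannot be undone once it has happened.

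**What to change.** For blocks not yet used:
1. Drop size 2 and use larger sizes in random order, for example 4, 6 and 8.
2. Do not disclose the new sizes to sites or in public documents until recruitment ends; state only that permuted blocks of varying size are used. This part is essential, because larger blocks with known sizes still allow 66-67% correct guesses.

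The cost is a new allocation table in REDCap. The sample size does not change. The largest possible imbalance in an unfinished block rises from 6/2 = 3 to 8/2 = 4 patients per stratum, which matters little against a total of 340.

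Locking the eligibility and equipoise form before the allocation is requested is optional. It prevents changes after the arm is seen, but does not stop somebody who predicts the arm from declining a patient beforehand.

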**Fig. 1 Fig1:**
[figure not shown]
Flowchart of inclusion and obtaining consent by the surgical equipoise

**Fig. 2 Fig2:**
[figure not shown]
CONSORT flow diagram

In cases where the surgeon finds that the allocated treatment may be contraindicated or is judged to harm the patient, it will be left to the surgeon's discretion to choose the most appropriate treatment. In cases where the bowels are left stapled in discontinuity as a part of the damage control principle, the patient's fascia cannot be closed due to swelling or the presence of abdominal compartment VAC treatment may be applied irrespective of the randomisation. These patients remain in the trial for an intention-to-treat and per-protocol analysis. By excluding such patients, there might be a risk of selection bias. Any eligible patient not included will be registered in a screening log.

### Preoperative patient assessment

The patients are preoperatively assessed according to Sequential Organ Failure Assessment (SOFA) to determine the degree of organ dysfunction [46].

### Interventions

#### Vacuum-assisted closure

The VAC® Abdominal Dressing System (KCI Vacuum Assisted Closure, San Antonio, TX, USA) will be used [44]. A video illustrating the procedure is attached in the supplementary material (Additional File 1). Intestines, including lateral aspects, are covered by the visceral protective layer. The first layer of foam is placed in the laparostoma on top of the visceral protective layer and must extend below the fascia at a distance of 5 cm from the fascial opening. Above this, a minimum of one piece of foam is folded and placed in the laparostoma. Finally, the laparostoma will be covered by the occlusive drape. A circular opening of approximately 5 cm in diameter will be created in the drape where the connection tubes to the vacuum pump will be placed. Simultaneously, while applying the negative pressure of 125 mmHg, the wound edges are approximated manually towards the midline. The dressing will be changed at an interval of approximately 48 h as standard or whenever needed according to the clinical condition. Each dressing change must be performed with the patient under general anaesthesia and muscle relaxation in the operating theatre. Peritoneal fluid must be cultured at each dressing change and when the fascia is closed. The fascial closure can, in some instances, be difficult due to swelling or the physical inability to close the abdomen. It must commence as soon as possible, judging by intra-abdominal findings, gastrointestinal function, and renal function. The aim will be to close the abdomen within eight days after the index operation.

The fascia closure after VAC treatment can be according to Israelsson's principle, as described below, or at the surgeon's discretion. A staged closure may start distally, proximally, or in combination. To ensure the uniformity of intervention in the arm receiving the open management, we have produced a video where the application of the VAC system is demonstrated in a step-by-step manner, as well as providing training for centres not familiar with the technique.

#### Primary closure

The Israelsson principle includes a running suture of the fascia with a distance of 5 mm between the stitches of 5 mm and the distance to the fascial edge of 5–10 mm. Monofilament PDS 2–0 or equivalent is used [47]. The suturing is started cranially and caudally, and the sutures are tied with self-locking knots. Approximately four times as much suture material as the length of the wound must be used or more. The peritoneal fluid must be cultured at closure.

#### Relaparotomy on-demand (ROD)

The treating surgeon decides at daily rounds whether a ROD is required and should be guided by the patient's general condition, gastrointestinal function, renal function, imaging findings, drain findings, and inflammatory parameters. A planned relaparotomy will not be considered a complication.

#### Microdialysis

The intraperitoneal microdialysis catheter will be placed before the abdominal closure or before applying the VAC system. The microdialysis catheter (M-dialysis 63, Microdialysis AB, Stockholm, Sweden) will be introduced through the abdominal wall outside the laparostoma via a charrier ten split cannula and placed in the peritoneal cavity between small intestine loops. The catheter will be perfused by an isotonic perfusion fluid (Perfusion fluid CNS Dextran, Microdialysis AB, Stockholm, Sweden) via a small pump (Microdialysis CMA 106 pump, Microdialysis AB, Stockholm, Sweden) at a flow rate of 0.3 μl/min. The catheter will be anchored to the skin. Samples will be collected in vials at 6-h intervals for the first four postoperative days. Bedside analysis for lactate, glycerol, and pyruvate concentration will be made via the ISCUSflex Microdialysis Analyzer (Microdialysis AB, Stockholm, Sweden). After analysis, the samples will be stored at  − 80 °C to analyse cytokine and MMP concentrations.

### Postoperative patient assessment

Immediately after index operation, the surgeon fills out the baseline form containing patient characteristics, Charlson comorbidity index, aetiology and extent of the peritonitis, surgical procedure, Mannheims peritonitis index and classification of the OA according to Bjork's classification [48, 49]. Patients can be transferred postoperatively to the intensive care unit (ICU) or the ward at the discretion of the treating team. Upon arrival to either the ward or the ICU, Acute Physiology and Chronic Health Evaluation II (APACHE II) score must be obtained by the attending anaesthesiologist [46, 50]. SOFA-scoring and routine blood samples with CRP, bilirubin, creatinine, and platelets must be performed daily within the first seven days after index operation. Discharge from the ICU will be at the discretion of the attending intensivist and surgeon.

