## Background

Perforation of the gastrointestinal tract is the most common cause of secondary peritonitis [1, 2]. The underlying conditions may be appendicitis, anastomotic dehiscence, perforated diverticulitis, intestinal ischemia, or gastroduodenal ulcer, being the most common [3–7]. Faecal peritonitis is associated with high mortality and morbidity rate, with a reported 28-days mortality up to 20%, increasing to 32% at six-month follow-up [8]. Age, comorbidity, time to intervention, and the extent of peritonitis are important risk factors [7, 9–14]. A prerequisite for non-failure is sufficient source control, antibiotics, and in cases with organ dysfunction, postoperative intensive care treatment may be necessary [15–19]. Despite sufficient treatment, the risk of postoperative abdominal complications is high, and several patients may undergo a reoperation (s) to reveal and treat the complications. Another risk is the development of abdominal compartment syndrome. To manage this, three different strategies may be employed: a planned relaparotomy (PR), a relaparotomy on-demand (ROD), or the open abdomen (OA) principle [2, 5, 20–23]. A randomised controlled trial on PR versus ROD in patients with secondary peritonitis due to gastrointestinal perforation, including 232 patients, showed no significant difference in 1-year mortality (36% vs. 29%) and morbidity (44% vs. 40%) [20]. ROD resulted in significantly fewer relaparotomies and lower hospital-related healthcare costs.

A guideline [19] and consensus report [24] from the World Society of Emergency Surgery recommend ROD or VAC as the preferred treatment strategies for intra-abdominal infections with peritonitis and non-traumatic abdominal emergencies. The benefit of primary abdominal closure and ROD strategy is that patients do not require further scheduled operations. The risk is a delay in treatment for ongoing abdominal sepsis, other serious complications, and abdominal compartment syndrome, which may be difficult to recognise clinically in the severely ill patient [25–28]. Delays in treating severe complications might increase the risk of morbidity and mortality [9, 11, 14]. The advantages of VAC are a planned inspection of the abdominal cavity and the possibility to diagnose and treat potential or overt abnormalities on time. The risk is the development of enteroatmospheric fistula, difficulties in abdominal wound closure, and the development of an incisional hernia [29, 30].

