### Follow-up

At hospital discharge, the patients will be booked for follow-up after 12 months in the outpatient clinic for abdominal palpation and abdominal CT-scan with intravenous contrast and Valsalva manoeuvre. In addition, the SF-36 questionnaire will be completed at the 3- and 12-month follow-up.

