#### Data collection and participant timeline

The pre- and perioperative assessment will consist of: baseline data (sex, age, surgery date, height, weight, body mass index, ASA score, WHO performance score, smoking, alcohol consumption, presence of comorbidities, previous abdominal surgeries, and steroid use). Data for surgical findings include aetiology of disease, anatomical location of intestinal perforation, degree of contamination, surgical treatment, method of abdominal wall closure, and suture material used for abdominal wall closure. Postoperative monitoring consists of SOFA, APACHE II, CRP, VAC treatment duration, unplanned VAC change, and the number of laparotomies in the ROD group. A patient record review will be performed at the follow-up after one month, three months, one year, and five years (Fig. 3). All data will be stored in REDCap®, hosted by the Odense Patient data Explorative Network (OPEN).

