The interim analysis will be performed at 25%, 50%, and 75% of recruited patients on the primary outcome after 30-days to detect significant differences between groups at the earliest possible time, ultimately leading to the termination of the study. We have adjusted our power calculation to the interim analyses using the O'Brien–Fleming method. The study group will have access to the results of the interim analyses and may make the final decision to terminate the study.

All of the above analyses will be performed as both intention-to-treat (patients will be analysed according to their randomisation group) and per-protocol analysis (what actually happened). The main analyses will be performed as complete case analyses. Multiple imputations will impute missing values in a supplementary analysis, including baseline characteristics as predictors.

*P* values < 0.05 will be considered statistically significant. Statistical calculations will be performed using Stata software (version 15, Stata Corp LP, Texas, USA).

In the VACOR-Microdialysis sub-study, the parameters will be compared using descriptive statistics for continuous and discrete variables. Repeated measurement across time points will be compared by mixed-effects regression models, including the interaction between time points and operation method and a random intercept for each patient. In addition, normality assumptions will be graphically assessed using quantile–quantile plots.

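### Complete-case analysis of SOFA and CRP over days 1 to 7 may be biased, because values can be lost through early discharge or death, and early discharge may differ between the arms

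*Protocol article*

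**What the plan says.** The Objectives section of the protocol article lists SOFA and CRP in the first seven days after the index laparotomy among the secondary outcomes. Under Postoperative patient assessment, SOFA scoring and routine bloods "must be performed daily within the first seven days after index operation". The same section covers both ward and ICU patients: "Patients can be transferred postoperatively to the intensive care unit (ICU) or the ward at the discretion of the treating team".

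After discharge, the next contacts described are later than that week. Under Follow-up: "At hospital discharge, the patients will be booked for follow-up after 12 months in the outpatient clinic", with SF-36 at 3 and 12 months. Under Data collection and participant timeline: "A patient record review will be performed at the follow-up after one month, three months, one year, and five years".

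Under Statistical analysis: "The main analyses will be performed as complete case analyses". No outcome is exempted. Multiple imputation is a supplementary analysis, and baseline characteristics are the only predictors named. No model is named for SOFA or CRP; the general line on continuous variables gives a Wilcoxon rank-sum test. A mixed-effects model for repeated measurements is planned only for the microdialysis sub-study.

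The arms differ in what ties a patient to hospital. For VAC: "The dressing will be changed at an interval of approximately 48 h as standard or whenever needed according to the clinical condition", each time in theatre under general anaesthesia, and "The aim will be to close the abdomen within eight days after the index operation". For ROD, the Background says: "The benefit of primary abdominal closure and ROD strategy is that patients do not require further scheduled operations".

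**The concern.** A complete-case comparison is safe only if the patients with values represent those without. Here there are two ways to lose values, and both are informative. A patient discharged alive before day 7 has probably recovered well, and the article describes no way of obtaining a later score. A patient who dies before day 7 was among the sickest. The treatment schedules make early discharge plausibly less common under VAC, so the first loss may depend on the arm. The second may too, but nothing in the article says how.

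Imputation from baseline characteristics would not repair this. What explains the missing value is the postoperative course, and that is not a baseline variable.

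At stake is a comparison that readers will use to judge mechanism. The Discussion cites animal and in silico work suggesting that VAC suppresses systemic inflammation and prevents multi-organ failure. SOFA and CRP are the clinical measures in the main study that speak to that claim.

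**Working it through.** The article gives no effect size, SD, discharge rate or length of stay for SOFA or CRP, so there is no stated figure to reproduce. The check asks how large the discharge bias could be when there is no true treatment effect.

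**Inputs from the article.** Seven-day window; complete-case main analyses; dressing changes about every 48 h; closure target of eight days, which spans the window; no scheduled reoperation under ROD.

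**Inputs assumed.** Share discharged by day 7: 10-40% in ROD and 0-10% in VAC. Correlation r between readiness for discharge and the SOFA or CRP value: 0, 0.4 or 0.8.

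**Model.** Readiness for discharge and the outcome are standard normal with correlation r. The healthiest share d of an arm leaves by day 7, and only the others are analysed. The mean of those who remain is then too high by r × L(d) SD, where L(d) = φ(z_d)/(1 − d), z_d is the normal quantile of d and φ is the normal density. The spurious difference, ROD minus VAC, is r × [L(d_ROD) − L(d_VAC)]. A positive value makes ROD look worse.

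L(0) = 0; L(0.05) = 0.109; L(0.10) = 0.195; L(0.20) = 0.350; L(0.30) = 0.497; L(0.40) = 0.644.

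| Discharged by day 7, ROD vs VAC | L difference | r = 0 | r = 0.4 | r = 0.8 |
|---|---|---|---|---|
| 10% vs 0% | 0.195 | 0 | 0.08 | 0.16 |
| 20% vs 5% | 0.241 | 0 | 0.10 | 0.19 |
| 30% vs 5% | 0.388 | 0 | 0.16 | 0.31 |
| 40% vs 10% | 0.449 | 0 | 0.18 | 0.36 |
| 10% vs 10%, or 30% vs 30% | 0 | 0 | 0 | 0 |

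A simulation with 400,000 patients per arm gave the same values within 0.005 SD.

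**Scale.** Under Sample size and power, the article gives 0.32 SD as the difference in mean CCI detectable with 80% power. The top of the range above is of that order; the bottom is about a quarter of it (0.08/0.32 = 0.25).

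**Deaths.** The same formula applies with the opposite sign when the sickest patients are lost. If the sickest 10% of the ROD arm died before day 7 in addition to the healthiest 10% leaving, the two losses would cancel by symmetry and that arm's mean would not shift. More early deaths than early discharges in ROD would turn the bias against VAC. The article gives mortality at 28 days and later, not at day 7 by arm, so the net sign cannot be worked out.

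**The case against.** The strongest reply is that much of this is inference. The article makes daily scoring mandatory without limiting it to inpatients. It names no SOFA or CRP model, and complete case could mean using each day's observed values. It says most patients are expected to be septic, so discharge within a week of an acute laparotomy may be uncommon. Eight days is a target for closure, not a fixed stay, and some patients allocated to ROD may receive VAC. The wording on imputation does not exclude further predictors. Details of a secondary outcome may sit in an analysis plan that is not shown.

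Most of this stands as a limit on what can be concluded. It does not remove the point, because the complete-case rule is stated, applies to the main analyses without exception, and sits beside a follow-up schedule with nothing between discharge and one month. Using each day's observed values would still compare different survivors and inpatients from day to day.

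Three stronger readings are tempting and are not supported:

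- That SOFA and CRP exist only for patients still in hospital. The text does not say so; it only describes no way of getting them afterwards.
- That the bias favours VAC by a known amount. No discharge rate is documented, and early deaths can offset or reverse the direction.
- That ward patients cannot have a full SOFA because the blood list contains no arterial oxygen value. SOFA scoring is required in its own right, and the list is not presented as its full set of inputs.

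**Conclusion.** The concern holds as a risk of bias in one secondary outcome. The stated complete-case rule does not suit a seven-day series in which values can be lost through recovery or death and in which time in hospital plausibly differs by arm. Imputation limited to the named baseline predictors would not correct it.

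The net direction and size are unknown. The discharge component is zero if early discharge is rare, equal between arms or unrelated to SOFA and CRP. It is about 0.1 to 0.4 SD against ROD with 10-40% against 0-10% discharged and a correlation of 0.4 to 0.8. Those rates and correlations are assumptions, and deaths come on top. The primary outcome does not use these daily values and is unaffected. The change is worth making, but the trial's main conclusion does not depend on it.

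**What to change.** For SOFA and CRP:

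1. Replace the complete-case rule with a mixed-effects model on all available daily values from all randomised patients, as already planned for the microdialysis measurements.
2. In the supplementary imputation, add postbaseline SOFA and CRP values and discharge status to the predictors.
3. Pre-specify one rule for days after discharge alive and for days after death, for example best rank and worst rank in the rank-sum comparison, and vary it in a sensitivity analysis.
4. Report by arm and day how many patients have a value, were discharged alive or had died. This shows readers how much the rule matters.

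The cost is analysis wording only; it uses data that the trial already collects. The downside is that any scoring convention for discharged and deceased patients is itself an assumption, which is why the sensitivity analysis belongs with it.
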